# Optimizing Protein Intake and Nitrogen Balance (OPINiB) in Adult Critically Ill Patients: A Study Protocol for a Randomized Controlled Trial

**DOI:** 10.2196/resprot.7100

**Published:** 2017-05-09

**Keywords:** nitrogen balance, protein requirements, catabolism, mechanical ventilation, intensive care unit

## Abstract

**Background:**

Adequate nutrition of critically ill patients plays a key role in the modulation of metabolic response to stress.

**Objective:**

This paper presents the development of a protocol for a randomized controlled trial (RCT) aimed at comparing clinical outcomes of patients in the intensive care unit (ICU) administered with standard and protein-fortified diet. Together with the RCT study protocol, the results of the observational analysis conducted to assess the feasibility of the RCT are presented.

**Methods:**

An RCT on adult patients admitted to ICU and undergoing mechanical ventilation in the absence of renal or hepatic failure will be conducted. Patients enrolled will be randomized with an allocation rate of 1:1 at standard diet versus protein-fortified diet. The estimated sample size is 19 per arm, for a total of 38 patients to be randomized.

**Results:**

Enrollment began in January 2017. In the feasibility study, 14 patients were enrolled. Protein administration increased significantly (*P*<.001) over time but was significantly lower compared to that recommended (*P*<.001). Blood urea nitrogen significantly increased (*P*<.03) over the period of observation. Such increased catabolism resulted in negative cumulative nitrogen balance (NB) in all patients, and some patients presented with a more negative NB compared to the others.

**Conclusions:**

Results of the feasibility study clearly confirmed that protein provision in ICU patients is below that recommended and that this results in impaired NB. The emerging of an interindividual variability in NB will be further analyzed in the RCT.

**Trial Registration:**

ClinicalTrials.gov NCT02990065; https://clinicaltrials.gov/ct2/show/NCT02990065 (Archived by WebCite at http://www.webcitation.org/6prsqZdRM).

## Introduction

In recent years, several studies have focused on the molecular and biological effects of nutrients in maintaining homeostasis in patients admitted in intensive care unit (ICU), and ad hoc recommendations have been developed for the assessment and provision of nutritional support in adult critically ill patients [1,2]. In such patients, specific metabolic mechanisms are activated to face stresses related to critical conditions (eg, trauma and sepsis). These metabolic responses consist of changes in substrate utilization and substance synthesis rates, as well as catabolism and hypermetabolism, resulting in increased energy expenditure, hyperglycemia, loss of body mass, and eventually psychological and behavioral problems [3]. Given such framework, monitoring the metabolic response is crucial in the management of ICU patients. However, this represents a major clinical challenge since it is generally assessed indirectly using nonspecific clinical and biochemical markers such as secondary infections, muscle atrophy and weakness, respiratory insufficiency, delayed wound healing, and incidence of secondary complications indicating prolonged catabolism [4]. Adequate nutrition plays a key role in the modulation of metabolic response to stress, contributing to the prevention of oxidative cellular injury and positively modulating immune responses.

All patients admitted in ICU require a full nutritional assessment for determining both energy and protein requirements to prevent malnutrition. According to international guidelines [2], the best approach is to reach the energy goal by indirect calorimetry (IC) when available. In the absence of IC, a predictive formula or simple weight-based equation (25-30 kcal/kg/day) may be used to determine energy requirements [2]. Although no consensus has been reached about the most accurate formula to be used in ICU, the Harris-Benedict equation (HBE) is the most often employed to estimate the resting energy expenditure (REE) in ICU patients [5]. However, these equations suffer from several limitations, including poor accuracy. Their poor accuracy is related to the fact that the variables affecting energy expenditure in critically ill patients (eg, weight, medications, treatments, and body temperature) are sensitive to changes over time. For mechanically ventilated patients in ICU, the main factors influencing REE have been found to be weight, height, body temperature, and minute ventilation [6].

In the critical setting, protein is the macronutrient most often lacking in such patients, and its supplementation is likely to result in beneficial effects [7]. Disorders of protein metabolism are documented as physiologic responses to stressful events and are reflected by important nitrogen loss and muscle wasting, which are proportional to the severity of illness [8]. Current evidence supports the early administration of protein supplementation because a stressful event alters homeostatic balance, resulting in an increased protein catabolism [9]. Administering exogenous protein or amino acid is crucial to reduce the breakdown of endogenous proteins by providing an alternative source of amino acids for gluconeogenesis and protein synthesis. Protein-energy deficit is associated with an increased rate of infection, poor wound healing, reduced respiratory muscle mass, and delayed weaning from mechanical ventilation, resulting in increased length of stay in ICU and increased care costs [10]. A high protein intake, estimated using a weight-based equation (1.2-2 g/kg/day), is recommended during the ICU stay regardless of the simultaneous caloric intake [9,11].

This paper presents the development of a protocol for a randomized controlled trial (RCT) aimed at assessing changes of nitrogen balance (NB) in ICU patients administered with standard parenteral/enteral diet and protein-fortified parenteral/enteral diet. Together with the study protocol, results of the pilot study conducted to assess the feasibility of such a trial are also presented.

## Methods

### Randomized Controlled Trial

#### Study Design and Randomization

This study has been designed as a parallel arm RCT enrolling patients admitted at the Department of Anaesthesia and Intensive Care *–* Azienda Sanitaria Universitaria Integrata di Udine (Italy). Medical and surgical adult patients admitted to ICU undergoing mechanical ventilation at the time of admission or in the first 12 hours will be enrolled. See Textbox 1 for selection criteria.

Selection criteria.Inclusion criteria:Aged 18 years and olderReceiving parenteral nutrition or enteral nutritionHaving an indwelling catheterUndergoing mechanical ventilationExclusion criteria:Current or 6-month past history of gastrointestinal bleedingbody mass index <18.5 kg/m^2^ or ≥ 30 kg/m^2^Terminal illnessPregnancyAcute renal failure defined using Kidney Disease Improving Global Outcomes (KDIGO) Clinical Practice Guidelines [12]: patients with a KDIGO stage 2 (serum creatinine 2-2.9 times baseline or urine output <0.5 mL/kg/h for 12 hours) and 3 (increase in serum creatinine ≥4 mg/dL, anuria for more than 12 hours, or starting of renal replacement therapy)Hepatic failure

Patients enrolled will be randomized to standard nutritional care (standard diet) to meet daily patient caloric requirement (control group) or appropriate amount of protein feeding (protein-fortified diet) to meet daily patient protein requirement (intervention group). Random allocation will be performed using a computer-generated algorithm (with an allocation rate of 1:1). Subjects enrolled will remain in the study until they are no longer mechanically ventilated. Participants will be blinded to treatment allocation. The flowchart of the study protocol is shown in Figure 1.

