#### Data Collection

Age (years), gender, weight (kg), height (cm), body mass index (BMI) (kg/m^2^), main diagnosis, clinical history, and illness severity assessed using the Acute Physiology and Chronic Health Evaluation (APACHE) II score [15] will be collected at time of admission in ICU (baseline assessment). The Simplified Acute Physiology Score (SAPS) II for mortality prediction in ICU [16] will also be calculated.

The following parameters will be recorded at midnight of each day: caloric intake, protein intake, measurement of 24-hour urine urea nitrogen (UUN) excretion, blood creatinine, NB, blood urea nitrogen (BUN) level, average blood glucose, amount of propofol administered (mL/day), amount of dextrose administered (mL/day).

A standard formula will be used for NB calculation [17,18]: total protein intake (g)/6.25 –(UUN + 4 g), where 6.25 = 6.25 g of protein per gram of nitrogen, UUN = grams of nitrogen excreted in the urine over 24-hour period of time, and 4 = 4 g of nitrogen lost each day as insensible losses via the skin and gastrointestinal tract. Additionally, for each patient, the duration of mechanical ventilation and any infection or skin alteration discovered during the study period will be reported.

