### Feasibility Study

#### Study Design

An observational analysis was conducted to assess the feasibility of the trial. This observational study enrolled patients admitted to the ICU *of* the Department of Anaesthesia and Intensive Care *–* Azienda Sanitaria Universitaria Integrata di Udine (Italy). The study was undertaken in a group of mixed medical, surgical, and trauma patients undergoing mechanical ventilation. Exclusion criteria were age (less than 18 years), chronic renal (identified using KDIGO recommendations) or hepatic failure, current or 6-month past history of gastrointestinal bleeding, body mass index <18.5 kg/m^2^or ≥30 kg/m^2^, terminal illness, and pregnancy. This study aimed at investigating the level of energy intake (kcal and protein) and nitrogen excretion in an ICU population receiving standard diet.

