#### Data Collection

Using REDCap, the following patient information were collected: admission diagnosis, comorbidities, age, sex, BMI, APACHE II score, SAPS II score (at baseline), type and amount of nutrition received (both caloric and protein intake), amount of propofol and dextrose (mL/day) administered, and blood chemistry (urea nitrogen level, creatinine, glucose) (at midnight of each day). A daily 24-hour urine collection was conducted in all patients and NB was calculated. For each patient, any infection or skin alteration occurring during the study period was reported. Daily data were collected until the end of mechanical ventilation or until renal/hepatic acute failure, death, or discharge from the ICU.

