### Feasibility Study

Sample characteristics are summarized in Table 1. A total of 14 patients were enrolled, with a median age of 48 years. Median weight was 83 kg, and median BMI was 25.5 kg/m^2^. For about a half of the patients (6/14, 43%) the main diagnosis reported at time of admission was trauma (especially multiple trauma). Of the 14 patients evaluated, 8 (57%) completed the observation until the end of mechanical ventilation.

Figure 2 shows the contribution of EN, PN, extra proteins (represented by albumin), and propofol and dextrose infusions to the mean energy (kcal) intake over the feasibility study period. During the first 3 days of observation, propofol contributed to about half of the daily caloric intake. Additionally, calories introduced by PN increased over the days, while calories provided by EN remained stable. Overall, caloric intake increased over time. Along with caloric intake, protein administration also increased significantly (*P*<.001) over the period of observation (Figure 3).

Despite the increased provision of protein during hospitalization, the BUN significantly increased (*P*=.03) over the period of observation (Figure 4), thus indicating an increased catabolism in patients enrolled (since urea represents the waste product from protein metabolism). Increased catabolism resulted in negative NB, as shown in Figure 5. All patients had a negative cumulative NB in the first 72 hours of observation, and some patients presented with a markedly more negative NB compared to the others.

Finally, Figure 6 reports the comparison between patients’ actual protein intake and that recommended by international guidelines (considering a value of 1.8 g/kg/day in the range between 1.2 and 2 g/kg/day). Clearly, the amount of protein actually administered is significantly lower compared to that recommended (*P*<.0001) (for patient 7, PN/EN was not administered in the first 24 hours due to medical procedures, resulting in fasting). The median difference between actual and recommend protein intake was found to be –360 g/kg (range –638 to 52).

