**Exit study, n (%)**			
	Transfer to another hospital		2 (14)
	Term of mechanical/spontaneous breathing		8 (57)
	Acute renal or hepatic failure		3 (21)
	Death		1 (7)

^a^BMI: body mass index.

^b^APACHE: Acute Physiology and Chronic Health Evaluation.

^c^SAPS: Simplified Acute Physiology Score.

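### As the exit rule is written, nitrogen balance measured after acute renal failure can enter the primary analysis, where it is falsely raised and pulls the arm difference toward the intake difference

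*Protocol article*

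**What the plan says.** - **RCT exit rule** (Methods, Study Design and Randomization): "Subjects enrolled will remain in the study until they are no longer mechanically ventilated". No other exit is named. Renal failure appears only among the exclusion criteria in Textbox 1.
- **Endpoint** (RCT Data Collection): NB is recorded every day as protein intake/6.25 − (UUN + 4 g), with "UUN = grams of nitrogen excreted in the urine over 24-hour period of time". The formula has no term for urea retained in the blood or removed by renal replacement.
- **Primary analysis** (Statistical Analysis Plan): a t test on NB in the ITT population at alpha .025.
- **Pilot stop rule** (Feasibility Study, Data Collection): "Daily data were collected until the end of mechanical ventilation or until renal/hepatic acute failure, death, or discharge from the ICU".
- **Pilot experience** (Feasibility Study results and Table 1): of 14 patients, "8 (57%) completed the observation until the end of mechanical ventilation". Three (21%) left under the heading "Acute renal or hepatic failure".

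**The concern.** NB measures net nitrogen only while the kidney excretes the nitrogen that the patient loses. With working kidneys and no benefit from extra protein, the extra nitrogen given reappears in the urine and cancels out of the formula. When excretion falls, or nitrogen leaves by renal replacement, it no longer cancels. NB then rises without any anabolic gain, and it rises more in the arm that receives more protein. Randomization does not remove this, because the error depends on intake, and intake is what the arms differ in.

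The pilot used the same 24-hour urine method and ended data at this event. The RCT text does not carry that stop over. What is at stake is a primary endpoint shifted toward the protein-fortified diet by days on which the measurement is not valid.

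**Working it through.** **1. The plan's own figure.** Inputs from Sample Size: difference 6 g, SD 5 g, alpha .025, power 0.90. A two-sample t test (noncentral t, two-sided .025) needs 19 per arm and has power 90.8%. The stated 19 per arm reproduces.

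**2. How often.** 3/14 = 21.4%, exact 95% CI 4.7% to 50.8%. The table does not separate renal from hepatic failure, so the renal share is unknown.

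**3. Intake-only gap.** If UUN approaches 0, NB = protein/6.25 − 4, and the arm difference equals the difference in nitrogen intake. Weight is the pilot median of 83 kg; targets and formulae are from Treatment Arms. It is assumed that each arm reaches its target, with control protein from enteral formula only.

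| Arm | Case | Protein (g/day) | Nitrogen (g/day) |
|---|---|---|---|
| Control | 20 kcal/kg, 1.5 kcal/mL, 40 g/L | 83×20/1.5×0.040 = 44.3 | 7.1 |
| Control | 25 kcal/kg, 1 kcal/mL, 40 g/L | 83×25/1×0.040 = 83.0 | 13.3 |
| Intervention | 1.2 g/kg | 99.6 | 15.9 |
| Intervention | 2 g/kg | 166.0 | 26.6 |

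Smallest gap: 15.94 − 13.28 = 2.7 g. Largest gap: 26.56 − 7.08 = 19.5 g.

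**4. Shift in the arm difference.** With a fraction f of patients fully affected, shift = f × (intake gap − true effect).
- No true effect, f = 3/14: 2.66 × 3/14 = 0.6 g; 19.48 × 3/14 = 4.2 g.
- Illustration with a true effect of 6 g and an assumed intake of 1.48 versus 0.8 g/kg: gap = 0.68 × 83/6.25 = 9.0 g; shift = (9.0 − 6) × 3/14 = about 0.65 g. With no true effect the same gap gives 9.0 × 3/14 = 1.9 g.

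These are upper cases: they take UUN as 0 and every analysed day as affected. Patients enter without the excluded stages of acute renal failure, so only days after onset count.

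**5. Effect on the test.** Simulation with 19 per arm, SD 5 g and no true effect. Each patient is affected with probability f; NB in affected patients rises by an assumed 5 or 10 g in both arms, plus an intake gap of 2.7 to 10.6 g in the intervention arm. False positives in favour of the intervention:
- f = 3/14: about 2.1% to 8.2%
- f = 1/14 (assumed lower renal share): about 1.5% to 2.4%

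The nominal rate is 1.25% per side.

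**6. Reserve in the sample size.** By the same calculation, 18 per arm gives 89%. If 3/14 of patients had no usable NB at all, 19 × 11/14 = about 15 per arm would remain, giving 81%.

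**The case against.** The strongest reply is that no sentence says NB from patients in renal failure will be used. The exit rule is one line in a condensed article. Read as exhaustive it would also retain patients who die or are transferred, so it is evidently a summary. The flowchart is not shown, and a full protocol or SAP may contain a censoring rule. This stands: use of those days is inferred from the exit rule, daily recording and ITT read together. It does not remove the point. The rule is stated rather than left open, and the same article spells out the additional stops for the pilot.

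Three stronger readings are tempting and are not supported.
- *NB becomes a pure intake measure.* This holds only as UUN nears 0. Stage 2 as described in Textbox 1 can rest on a rise in creatinine or reduced urine output, neither of which means zero urinary nitrogen. Partial failure inflates NB in part.
- *The 90% power is wrong.* It is correct on its inputs.
- *The trial suffers both bias and lost power through missing patients.* These are alternatives. Patients whose later days are used are not lost. Patients whose NB ends at onset still have earlier days, so 81% is a worst case.

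It is also fair to say that ending measurement at a post-randomization event carries its own risk of bias.

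**Conclusion.** The point holds as a conflict between two stated rules with a specific consequence for the primary endpoint. Followed as written, the RCT admits NB from days on which the formula overstates balance, and the error moves the arm difference toward the intake difference. With no true effect, that favours the protein-fortified arm.

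The ceiling of 0.6 to 4.2 g, against a 6 g target, rests on the pilot's pooled 3/14 rate, a weight of 83 kg, intake at target, UUN of 0 on all analysed days and no true effect. The likely size is smaller and cannot be fixed from the article, because neither the renal share nor the proportion of affected days is given. The sample size needs no correction on this ground; it is enough to note that 19 per arm leaves no reserve.

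**What to change.** 1. Reconcile the RCT exit rule with the pilot's stop rule for data. State that NB values used in the primary analysis end at onset of acute renal failure, by the trial's own definition, or of renal replacement. This concerns which measurements are analysed, not patient care. Say whether hepatic failure is handled the same way, as it was in the pilot.
2. Keep affected patients in the ITT t test through their NB before onset, for example as the per-patient mean of valid days.
3. Report the number affected in each arm.
4. Add a sensitivity analysis using all recorded days.
5. As a minor clarification, align the renal wording. The abstract refers to absence of renal or hepatic failure and Textbox 1 excludes acute renal failure, while the pilot excluded "chronic renal (identified using KDIGO recommendations) or hepatic failure". As summarized in Textbox 1, a creatinine of 3 or more times baseline that meets neither the 4 mg/dL criterion nor any urine-output or replacement criterion fits neither listed stage.

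The cost is wording in the protocol and SAP and one extra analysis, with no additional patients. The downside is fewer days for each affected patient and truncation at a post-randomization event, which is why items 3 and 4 belong with the change.

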**Figure 1 figure1:**
[figure not shown]
Flowchart of the study protocol.

#### Treatment Arms

The standard diet consists of an energy goal based on weight formula (20-25 kcal/kg/day). According to the ICU nutritional protocol, enteral nutrition (EN) will be started at an initial rate of 10 mL/h and increased by 20mL/h every 12 hours in the absence of significant gastric residuals (<250 mL), with the aim of reaching the energy goal within 72 hours of admission. The EN formulae used are standard (1-1.5 kcal/mL, 40 g/L protein). If EN is not tolerated or not indicated, supplemental parenteral nutrition (PN) will be used to make up the energy shortfall. The PN formula used is standard (1000 kcal/L, 37 g/L protein).

The protein-fortified diet consists of an energy goal based on REE and a protein target based on the most recent literature recommendations (1.2-2 g/kg/day) [2]. Daily caloric requirement and subsequent protein content for patients enrolled in the intervention group will be calculated using formulae reported in Multimedia Appendix 1 [10,13,14]. For each patient, it will be calculated based on the REE and the daily protein requirement (1.2-2 g/kg/day of body weight registered at time of admission) and the corresponding caloric intake (1 g=4 kcal). Daily total caloric intake will be represented by 50% protein (1 g=4 kcal) and another 50% nonprotein (ie, fat and carbohydrates).

For the intervention group, EN will be started at an initial rate of 10 mL/h and increased by 20 mL/h every 8 hours in the absence of significant gastric residuals (<250 mL) with the aim of reaching the energy goal within 48 hours of admission. The EN formulae used are high in protein (1-1.5 kcal/mL, 74 g/L protein). If EN is not tolerated or not indicated, supplemental PN is used to make up the energy shortfall. The PN formula used will be arranged by the hospital pharmacy to meet the energy targets set for the intervention group.

For patients enrolled in the control group and the intervention group, gastric residuals will be checked 4 times per day and electrolytes will be closely monitored and replaced. Adequacy of nutritional support will be determined daily by measuring NB.

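### The intervention arm's g/kg protein target, 50% protein rule and listed enteral feeds do not fit together, and its feeding steps are worded on energy, so protein can stay below 1.2 g/kg/day with no stated response

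*Protocol article*

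**What the plan says.** All of this is in the protocol article, under Methods, Randomized Controlled Trial.

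- **Purpose of the arm** (Study Design and Randomization): "appropriate amount of protein feeding (protein-fortified diet) to meet daily patient protein requirement (intervention group".
- **Prescription** (Treatment Arms): the energy goal comes from resting energy expenditure (REE) and the protein target is 1.2-2 g/kg/day. "For each patient, it will be calculated based on the REE and the daily protein requirement". The formulae are in Multimedia Appendix 1, which is not shown.
- **Composition** (Treatment Arms): "Daily total caloric intake will be represented by 50% protein (1 g=4 kcal", with the other half from fat and carbohydrate.
- **Feed** (Treatment Arms): "The EN formulae used are high in protein (1-1.5 kcal/mL, 74 g/L protein".
- **Delivery** (Treatment Arms): EN is stepped up "with the aim of reaching the energy goal within 48 hours of admission". Then: "If EN is not tolerated or not indicated, supplemental PN is used to make up the energy shortfall". For the parenteral product: "The PN formula used will be arranged by the hospital pharmacy to meet the energy targets set for the intervention group".
- **Monitoring**: nitrogen balance (NB) is measured daily as the check on adequacy (Treatment Arms), and protein intake is recorded daily (Data Collection). Neither section says what to do when protein is low.

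**The concern.** The two arms differ by aim: control is fed to a caloric requirement, intervention to a protein requirement. Yet the intervention arm's EN advance, PN top-up and pharmacy order are all worded on energy. A patient who tolerates full EN meets the energy goal, so the condition for PN never arises, whatever the protein intake.

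The 50% rule looks as if it would protect protein, but it has to agree with the g/kg target and be deliverable with the feeds named. If it does neither, staff hold two conflicting protein instructions with no order of precedence, and delivered protein is set by feed density and REE per kg.

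Protein dose is the experimental variable and protein intake is a term in the NB formula. The stake is whether the arm receives the treatment that defines it.

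**Working it through.** **Inputs.** From Treatment Arms: target 1.2-2 g/kg/day; 50% of calories as protein; 4 kcal per g; feed 74 g/L at 1-1.5 kcal/mL; control energy goal 20-25 kcal/kg/day. From the Introduction: "simple weight-based equation (25-30 kcal/kg/day) may be used to determine energy requirements". From Data Collection: 6.25 g protein per g nitrogen (N). From the feasibility results: median weight 83 kg, for illustration only.

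**Assumption.** No kcal/kg value is given for the intervention arm. I take 20-25 (the control range) and 25-30 (the Introduction's range).

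**Stated figures.** The protocol gives no figure for protein delivered at the energy goal, so there is none to reproduce. Its sample size does reproduce: a t test with difference 6 g, SD 5 g and two-sided alpha 0.025 has power 0.908 at 19 per arm. This point does not affect it.

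**Step 1. Protein share of the listed feeds.**
- 1.0 kcal/mL: 74 × 4 / 1000 = 29.6% of energy.
- 1.5 kcal/mL: 74 × 4 / 1500 = 19.7% of energy.

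Neither reaches 50%.

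**Step 2. The 50% rule against the g/kg target.**
- Protein implied by the rule = energy × 0.5 / 4. At 20 kcal/kg this is 2.5 g/kg; at 25 it is 3.125 g/kg. Both exceed the 2 g/kg ceiling.
- Energy at which the two agree = target × 4 / 0.5. For 1.2 g/kg this is 9.6 kcal/kg; for 2 g/kg it is 16 kcal/kg.
- At those low goals full EN still misses the floor: 0.71-1.18 g/kg at 1.0 kcal/mL and 0.47-0.79 g/kg at 1.5 kcal/mL.
- Share the g/kg target needs = target × 4 / energy: 24-40% at 20 kcal/kg, 19.2-32% at 25, 16-26.7% at 30.

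**Step 3. Protein once the energy goal is met on full EN.** Protein (g/kg) = energy (kcal/kg) / density (kcal/mL) × 0.074.

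| Energy goal (kcal/kg/day) | 1.5 kcal/mL | 1.0 kcal/mL |
|---|---|---|
| 20 | 0.99 | 1.48 |
| 22 | 1.09 | 1.63 |
| 24 | 1.18 | 1.78 |
| 25 | 1.23 | 1.85 |
| 30 | 1.48 | 2.22 |

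Energy needed for 1.2 g/kg: 1.2 / 0.074 = 16.2 kcal/kg at 1.0 kcal/mL, and × 1.5 = 24.3 at 1.5 kcal/mL. At a 20 kcal/kg goal, any feed denser than 20 × 0.074 / 1.2 = 1.23 kcal/mL falls short. The thinner feed passes the 2 g/kg ceiling above 2 / 0.074 = 27.0 kcal/kg.

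**Step 4. Shortfall at 83 kg on the 1.5 kcal/mL feed.** The floor is 1.2 × 83 = 99.6 g/day.
- 20 kcal/kg: 20 × 83 / 1.5 = 1107 mL, giving 81.9 g. Short by 17.7 g (17.7 / 6.25 = 2.8 g N).
- 22 kcal/kg: (1.2 − 1.085) × 83 = 9.5 g (1.5 g N).
- 24 kcal/kg: (1.2 − 1.184) × 83 = 1.3 g (0.2 g N).
- 25 kcal/kg and above: no shortfall against 1.2 g/kg.

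**The case against.** The strongest defence is that this is a condensed article and Appendix 1 is unseen. The prescription is built jointly from REE and protein, so the energy targets in the pharmacy sentence may mean that joint prescription. Staff holding a calculated g/kg target may also choose the thinner feed, which the text permits, and NB and protein intake are seen daily.

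Much of this stands. That no rule responds is shown only for the article text, and the shortfall needs both the dense feed and an energy goal below 24.3 kcal/kg. But Appendix 1 is titled as a calculation of intake, and a correct target does not by itself change delivery steps worded on energy. Nor can it remove the conflict printed in Treatment Arms between the 50% rule, the g/kg target and the feeds. The daily checks have no action attached.

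A reader might go further and infer that the missing protein trigger pulls the between-arm contrast below the planned 6 g of NB. The documents do not support that. Take urinary nitrogen as unchanged, so that the contrast in g N is the difference in protein intake (g/kg) × weight / 6.25. At 83 kg, with 1.5 kcal/mL in the intervention arm and 1.0 kcal/mL in control:
- At 25 kcal/kg in both arms the floor is already met (1.233 g/kg), yet the contrast is (1.233 − 1.0) × 83 / 6.25 = 3.1 g N. A top-up to 1.2 g/kg changes nothing.
- At 20 kcal/kg in both arms, a top-up to 1.2 g/kg gives (1.2 − 0.8) × 83 / 6.25 = 5.3 g N, still under 6.
- With 25-30 in intervention against 20-25 in control, the range is 3.1 (25 against 25) to (1.48 − 0.8) × 83 / 6.25 = 9.0 g N (30 against 20).

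With 1.5 kcal/mL in both arms at 20-25 kcal/kg, the contrast is 6.0-7.5 g N at 83 kg but 4.8-6.0 at 66 kg, the feasibility study's lower quartile. The contrast therefore depends mainly on how feed densities pair across arms and on body weight. The documents do not say which densities are paired.

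**Conclusion.** The point holds as a conflict between rules stated in the text. The 50% rule and the 1.2-2 g/kg target disagree at any energy goal above 16 kcal/kg/day, and neither end of the listed density range can supply 50% by EN. Because delivery is worded on energy, a patient can satisfy the stated steps and still miss the target that defines the arm.

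The size is moderate and conditional: up to about 18 g protein/day below the floor at 83 kg and 20 kcal/kg on the 1.5 kcal/mL feed, shrinking to nothing from 24.3 kcal/kg upward. It rests on full EN, the dense feed and an assumed energy goal. It does not show that intervention patients in general are underfed in protein, nor that the sample size or the planned 6 g difference is undermined.

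**What to change.** In Treatment Arms, for the intervention group:

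1. State that the patient's g/kg protein target takes precedence over the 50% rule, or delete the 50% rule.
2. Tie the choice of feed density, the top-up and the pharmacy PN order to the protein target as well as energy. When energy is met but protein is short, use the lower-density feed, or add an enteral protein supplement or parenteral amino acids. Keep the 2 g/kg ceiling in view with the thinner feed at goals above 27 kcal/kg.
3. If Appendix 1 already sets this, say so in the section.

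The cost is a few sentences and a change to the pharmacy order; no new data are needed. At 83 kg and 20 kcal/kg the burden is about 18 g/day of extra protein, or 20 × 83 / 1.0 = 1660 mL/day of the thinner feed in place of 1107 mL. Enrolment began in January 2017, data collection was expected to end in April 2017, and the article appeared in May 2017, so the change may reach few or no patients. In that case, report delivered g/kg protein and the feed density used in each arm.
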